## Abstract

**Background:**

Matching treatment based on tumour molecular characteristics has revolutionized the treatment of some cancers and has given hope to many patients. Although personalized cancer care is an old concept, renewed attention has arisen due to recent advancements in cancer diagnostics including access to high-throughput sequencing of tumour tissue. Targeted therapies interfering with cancer specific pathways have been developed and approved for subgroups of patients. These drugs might just as well be efficient in other diagnostic subgroups, not investigated in pharma-led clinical studies, but their potential use on new indications is never explored due to limited number of patients.

**Methods:**

In this national, investigator-initiated, prospective, open-label, non-randomized combined basket- and umbrella-trial, patients are enrolled in multiple parallel cohorts. Each cohort is defined by the patient’s tumour type, molecular profile of the tumour, and study drug. Treatment outcome in each cohort is monitored by using a Simon two-stage-like ‘admissible’ monitoring plan to identify evidence of clinical activity.

All drugs available in IMPRESS-Norway have regulatory approval and are funded by pharmaceutical companies. Molecular diagnostics are funded by the public health care system.

**Discussion:**

Precision oncology means to stratify treatment based on specific patient characteristics and the molecular profile of the tumor. Use of targeted drugs is currently restricted to specific biomarker-defined subgroups of patients according to their market authorization. However, other cancer patients might also benefit of treatment with these drugs if the same biomarker is present. The emerging technologies in molecular diagnostics are now being implemented in Norway and it is publicly reimbursed, thus more cancer patients will have a more comprehensive genomic profiling of their tumour. Patients with actionable genomic alterations in their tumour may have the possibility to try precision cancer drugs through IMPRESS-Norway, if standard treatment is no longer an option, and the drugs are available in the study. This might benefit some patients. In addition, it is a good example of a public–private collaboration to establish a national infrastructure for precision oncology.

*Trial registrations* EudraCT: 2020-004414-35, registered 02/19/2021; ClinicalTrial.gov: NCT04817956, registered 03/26/2021.

## Background

Curative treatment options for patients with metastatic solid tumors are still rare. Most diagnostic groups have standardized algorithms for evidence-based treatment, and when the patients progress on standard-of-care, inclusion in clinical studies is an option.

Although personalized patient care is not a new concept, precision cancer medicine, based on use of molecular testing to identify targetable alterations, represents a major development in the field. Findings based on these technologies have led to new paradigms of cancer treatment [1–5].

A high number of advanced solid tumours (30–80%) display potentially “actionable” genomic variants [6–8]. However, the clinical benefit of targeting these remains largely anecdotal. Less than 7% of cancer patients were estimated to benefit from genome-guided anti-cancer therapies in the US in 2018 [9]. Other studies using genomic profiling approaches with individualized matching of molecular variant and drug, report low inclusion rate and modest overall rate of clinical benefit [10], although much higher than the first generation precision medicine trials in oncology [11–13]. This is probably due to increasing knowledge about actionable genes and driver mutations in tumour development, resistance mechanisms, a more refined diagnostic work-up and availability of new targeted therapeutics [14].

There is an increasing demand for more clinical studies exploring precision cancer treatment. Methods for more extended molecular profiling are available, and a considerable number of drugs are already approved on specific indications. However, these drugs are restricted to be used within the approved indication. Some drugs targeting a specific pathway or gene aberration, might be efficient in other subgroups of patients, not yet fully investigated in clinical trials.

IMPRESS-Norway (NCT04817956) is a national investigator-initiated clinical study. The aim is to enhance knowledge about molecular variant-drug matches and harmonize access to genomic testing and off-label use of cancer drugs in Norway. Thereby, patients with advanced cancer will have access to extended molecular diagnostics and putatively also treatment based on the tumour characteristics. The study will use a combined umbrella and basket design and a Simon two-stage model of expanding cohorts to establish potentially effective combinations of biomarker and drug [15, 16].

The IMPRESS-Norway study design is based on the DRUP trial (Drug Rediscovery Protocol) which has been ongoing in the Netherlands for five years [17]. They treat patients with targeted drugs based on a molecular profile, and outside of their current market authorisation. The initial results from the DRUP-trial reveal a clinical benefit of 34% in the first 215 patients beyond 16 weeks [17, 18]. According to the study report, 46% of the patients that were referred after local genomic testing were included in the trial. Both the reported inclusion rate and overall rate of clinical benefit were higher than other studies of tumour molecular profiling with matched targeted treatment [8, 19]. Based on the success of the DRUP-trial, similar studies have been initiated in other European countries including Denmark, Norway, Sweden, and Finland [20].

There is a lack of data on drug safety and efficacy for rare indications outside of the approved label for many cancer drugs. Through this clinical study, where key clinical outcomes are systematically collected, missing data will be provided, and also benefit some patients by offering a new treatment line based on molecular profiling.

## Methods/design

Oslo University Hospital is the sponsor of the study. All hospitals in Norway with an oncology or haematology care unit participate; recruiting patients for molecular profiling and providing study-specific treatment to patients included in a study cohort. Patient recruitment started in April 2021, and by March 7, 2022, 298 patients have been enrolled.

### Study objectives

There are two primary objectives of the study. The first is to describe the anti-tumour activity and toxicity of commercially available, targeted anti-cancer drugs used for treatment of patients with advanced malignancy that harbours a genomic or expression variant known to be a drug target or to predict sensitivity to a drug. This will be measured by percentage of patients included/treated in a cohort defined by molecular profile, drug and cancer subtype with disease control at 16 weeks of treatment (stable disease or better). Treatment-related grade ≥ 3 side effects and serious adverse events will be monitored. The second primary objective is to facilitate patient access to commercially available targeted anti-cancer drugs of potential efficacy for treatment of an advanced malignancy that harbours a genomic or protein expression variant known to be a drug target or to predict sensitivity to a drug.

The secondary study objectives are as follows: (1) To further describe tumour response to treatment; (2) To perform extensive and longitudinal biomarker analyses, including (but not limited to) next generation sequencing [including whole genome and transcriptome sequencing (WGS and WTS respectively)], on a fresh tumour biopsy specimen and liquid biopsies (blood samples, effusions); (3) To map the patient journey through the Precision Cancer Medicine pipeline; and (4) To assess the availability of tumour tissue biopsy across and within tumour types.

The exploratory objectives are to study mechanisms of resistance by the use of serial fresh tumour biopsies for WGS/WTS and liquid biopsies; to evaluate clinical utility of circulating tumour DNA (ctDNA) in treatment decision procedures and in monitoring treatment response; to investigate response evaluation in cohorts with immunotherapy; to provide long term follow-up data on the patients; to investigate patient reported outcome measurements (including health-related quality of life); to investigate cost-effectiveness; to determine clinical course in patients not included in treatment cohorts; to explore other methods for response evaluation (Artificial Intelligence (AI) in radiology for instance); to investigate need for medical genetics expertise for follow-up of patients; and to investigate the ESMO Scale for Clinical Actionability of molecular Targets (ESCAT) guidelines for actionable targets.

### Study design

This is a prospective, non-randomized, open-label combined basket- and umbrella clinical study based on a Simon two stage model of expanding cohorts. This model, tested in the Targeted Agent and Profiling Utilization Registry (TAPUR) and DRUP studies, has been designed to effectively test a set of drugs using a precision medicine algorithm while minimizing the number of patients required [21].

Each tumour type/molecular variant/drug will define a specific cohort, and each cohort constitutes a Simon two stage trial model to identify cohorts with evidence of clinical activity. Stage 1 cohorts will enrol eight participants and will be considered positive if ≥ 1 show objective response or stable disease at 16 weeks of treatment. In case of a positive stage 1, a stage 2 will be initiated enrolling 16 additional participants into the cohort. If no patients experience disease control at week 16 (in stage 1), the cohort will be closed. Four or fewer responses out of 24 in the stage 2 cohort, will suggest a lack of activity, while five or more responses will suggest that further investigation of the drug in the tumour/variant cohort is warranted. For positive stage 2 cohorts, a stage 3 expansion cohort of up to 130 additional patients may be opened following agreements between the trial and the company providing the drug. Such expansion cohorts are organised like a phase 2 trial and as of February 2022, the four Regional Health Authorities in Norway have jointly decided that reimbursement of drug may be granted at the request of the trial for specific cohorts and for responding patients following evaluation at 16 weeks according to a pay for performance model. This in line with what has been set out in The Netherlands for the DRUP trial (PMID: 31038154).

For purposes of cohort definition, the ‘variant’ category can be defined at the level of the gene that harbours the mutation or overexpression (for instance HER2) or be determined by specific mutations (like BRAF V600E) or represent a profile (such as tumour mutational burden; TMB). Pan-cancer cohorts will be defined when the molecular subtype is very rare [15, 16].

### Available drugs in IMPRESS-Norway

Patients included for treatment in IMPRESS-Norway are treated with commercially available licenced drugs provided by participating pharmaceutical companies. This is a dynamic study design and will include more drugs as more pharmaceutical companies are participating. For every available drug though, additional drug-specific study information will be provided in separate amendments (drug-specific study manuals). These include the Summary of Product Characteristics (SmPC) and/or Investigator's Brochure (IB), drug-specific patient information in Norwegian, and a drug-specific study manual including drug-specific inclusion and exclusion criteria, risk benefit assessment and treatment schedules. Currently we have available a PDL1 inhibitor and several targeted therapies. Eight drugs were available (from Roche) when initiating the trial and new agreements have since been made with Novartis, Eli-Lilly and Incyte, providing additional drugs. We have also defined cohorts repurposing “old” generic drugs, which comes with a low cost, and covered by research funding (4 cohorts with 8 patients each).

### Combination

Drugs used in the study can either be used as monotherapy or as combinations approved by US Food and Drug Administration (FDA) or the European Medicine Agency (EMA). Each cohort will include one specific drug or one drug combination (approved) in one diagnostic subgroup. In selected cohorts, a study drug can be added to a standard backbone of systemic treatment after approvals from the involved pharmaceutical company and the Norwegian Medicines Agency.

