### Selected exclusion criteria—treatment phase

A potential participant who meets any of the following criteria for medical conditions will be excluded from inclusion in the molecular profiling.Patients with the following pre-existing cardiac diagnosis, uncontrolled angina, uncontrolled atrial or ventricular arrhythmias, or symptomatic congestive heart failure.Patients with left ventricular ejection fraction (LVEF) known to be < 40%.Patients with any other clinically significant medical condition which, contradicts participation in the study.Patients with known progressive brain metastases determined by serial imaging or declining neurologic function in the opinion of the treating physician. Patients with previously treated/stable brain metastases are eligible.Patients eligible to enter other ongoing trials which have the potential to benefit the patients equally or more than an IMPRESS-Norway cohort, and for whom access to the ongoing trials is manageable.Ongoing toxicity > Common Terminology Criteria for Adverse Events (CTCAE) grade 2, other than peripheral neuropathy, related to anti-tumour treatment that was completed within 4 weeks prior to treatment initiation. Patients with ongoing peripheral neuropathy of ≥ CTCAE grade 3.Patients with stroke (including transient ischemic attack (TIA)) or acute myocardial infarction within 4 months before the first dose of study treatmentIf the patient’s tumour has a genomic variant known to confer resistance to an anti-cancer agent available in this study, the patient will not be eligible to receive that agent but will be eligible to receive other drugs available in this study if all inclusion and exclusion criteria are met for that drugPatient is receiving any other anti-cancer therapy (cytotoxic, biologic, radiation, or hormonal other than for replacement) except for medications that are prescribed for supportive care but may potentially have an anti-cancer effect (e.g., megestrol acetate, bisphosphonates) or ongoing castration-intent therapy for prostate cancer. These medications must have been started ≥ 1 month prior to enrolment on this study. Patients may be on warfarin, low molecular weight heparin or direct factor Xa inhibitors.

Note: For each drug included in this protocol, specific inclusion and exclusion criteria (based on the Summary of Product Characteristics (SPC) or manufacturer’s recommendations) may also apply.

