### Statistical analyses

Admissible designs lie between MiniMax and Optimal designs and fits well for both (i.e. small maximum sample size, and low expected sample size under the null hypothesis of low activity). A true response rate (complete response [CR], partial response [PR], stable disease [SD]) of less than 10% will be considered of no clinical interest. A response rate of 30% or more will be considered of sufficient interest to warrant further study in a confirmatory trial.

Negative cohorts (no patients benefitting) will be closed. If one or more of the first eight patients benefit from treatment, an additional 16 participants who fulfil the inclusion criteria will be included in the cohort. Four or fewer responses out of 24 included in total, will suggest a lack of activity, while five or more responses will suggest that further investigation of the drug in the tumour/variant cohort is warranted. This monitoring rule has 85% power and an alpha error rate of 7.8%. These operating characteristics were selected to represent a reasonable compromise between high power, low false positive rates, and desire for small sample sizes.

When an individual cohort terminates accrual early or completes accrual, efficacy, and toxicity data in addition to patient characteristics will be summarised descriptively with tabulations, rates and confidence intervals.

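### In cohorts that add the study drug to a standard backbone, the stated 7.8% is the false-positive rate for the added drug only if the backbone alone gives 10% disease control at 16 weeks

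*Protocol article*

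**What the plan says.** **Scope of the rule.** The Study design section of the protocol article says that "each cohort constitutes a Simon two stage trial model to identify cohorts with evidence of clinical activity". It makes no exception for any type of cohort. Success is objective response or stable disease at 16 weeks of treatment.

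**The rule.** Under Statistical analyses, a true rate "of less than 10% will be considered of no clinical interest", and "A response rate of 30% or more will be considered of sufficient interest to warrant further study in a confirmatory trial". The response rate there includes stable disease. On continuing to stage 2: "If one or more of the first eight patients benefit from treatment, an additional 16 participants who fulfil the inclusion criteria will be included". Five or more successes among 24 are read as grounds for investigating the drug further in that tumour/variant group; four or fewer suggest no activity. The error rates are given once, for the rule as a whole: "This monitoring rule has 85% power and an alpha error rate of 7.8" per cent.

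**Backbone cohorts.** The Combination section allows some cohorts a further option: "a study drug can be added to a standard backbone of systemic treatment after approvals from the involved pharmaceutical company". Approval by the national medicines regulator is required as well. The section gives these cohorts no null rate, control or decision rule of their own.

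**Exclusion.** The selected exclusion criteria for the treatment phase rule out a patient who is "receiving any other anti-cancer therapy (cytotoxic, biologic, radiation, or hormonal other than for replacement"). The listed exceptions are supportive-care medication and ongoing castration-intent therapy for prostate cancer. A backbone is not among them.

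**The concern.** A single-arm test against a fixed null says something about a drug only if the null is the success rate expected when that drug does nothing. For a study drug given alone, the plan takes that rate to be 10%. When the drug is added to active systemic treatment, the rate with an inert drug is whatever the backbone achieves by itself. Because stable disease counts, a backbone can produce successes without shrinking any tumour.

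The rule still reads five or more successes as a finding about the study drug. If the backbone alone does better than 10%, an inactive drug has more than a 7.8% chance of a positive verdict. That verdict recommends further investigation and makes the cohort a candidate for a stage 3 expansion of up to 130 patients.

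**Working it through.** **Inputs from the article.** Null p0 = 10%, alternative p1 = 30%; stage 1 n1 = 8, close at 0 successes; total n = 24, positive at 5 or more; stated alpha 7.8% and power 85% (Study design; Statistical analyses).

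**Input not in the article.** The 16-week disease-control rate on the backbone alone. It is assumed here over 5% to 30%, so that values on both sides of the null are shown.

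**Formula.** For a true rate p and a final cutoff c,

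P(positive | p) = Σ (x = 1 to 8) P[Bin(8, p) = x] × P[Bin(16, p) ≥ max(0, c − x)].

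**Step 1: reproduce the stated figures (c = 5).** At p = 0.10:

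| x in stage 1 | P(x) | P(enough in stage 2) | product |
|---|---|---|---|
| 1 | 0.3826 | 0.0684 | 0.0262 |
| 2 | 0.1488 | 0.2108 | 0.0314 |
| 3 | 0.0331 | 0.4853 | 0.0160 |
| 4 | 0.0046 | 0.8147 | 0.0037 |
| 5 or more | 0.0004 | 1 | 0.0004 |

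The sum is 0.0778 before rounding of the terms. At p = 0.30 the same formula gives 0.857. The stated 7.8% and 85% are therefore correct for true rates of 10% and 30%.

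**Step 2: inert drug on a backbone.** If the added drug does nothing, p equals the backbone's own rate. Same rule, c = 5:

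| Assumed disease control on backbone alone | P(cohort called positive) |
|---|---|
| 5% | 0.5% |
| 10% | 7.8% |
| 12% | 14% |
| 15% | 27% |
| 20% | 51% |
| 25% | 72% |
| 30% | 86% |

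Below 10% the rule is stricter than stated. Above 10% the error climbs quickly: at 15% it is 26.5/7.8 ≈ 3.4 times the stated figure.

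**Step 3: a cutoff matched to a higher null, same 8 + 16 patients and same stop at 0 of 8.** Take p0 = 20% and p1 = 40% as an example.

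| Final cutoff | P(positive) at 20% | P(positive) at 40% |
|---|---|---|
| 8 or more of 24 | 8.8% | 80.3% |
| 9 or more of 24 | 3.6% | 67.0% |

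The cutoff of 8 comes closest to the present error rates. At a true rate of 30% it gives 43%, against 86% under the present cutoff of 5.

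**Step 4: the exclusion beside the Combination section.** Read literally, a patient already on a backbone is receiving anti-cancer therapy and no listed exception applies. Read in context, "other" may mean therapy outside the cohort's own regimen, in which case a backbone that belongs to the regimen is not excluded. The text does not say which reading is meant.

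**The case against.** **The 7.8% is not wrong.** It is the error rate at a true rate of 10%, and it reproduces exactly. A reader might infer that it fails in every backbone cohort. The article does not support that: it gives no backbone rate, and patients enter after progression on standard treatment, when they no longer benefit from it, or when none is available or indicated. Backbone-alone control could be 10% or lower. This stands, and it is why the point is conditional. It does not remove the point, because the entry criteria do not say that the backbone is a treatment the patient has already failed, and nothing in the article puts its rate at or below 10%.

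**The detail may sit elsewhere.** Backbone use is exceptional, needs outside approvals, and each drug has its own manual, which is not shown. A cohort-specific null could be set there or in the full protocol. But the article does not list decision rules among the contents of the manuals, and it states the rule for each cohort without exception. The issue is the scope of a stated rule, not a missing detail.

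**The consequence is limited.** A positive stage 2 only suggests further investigation, a confirmatory trial is named as the next step, stage 3 requires agreement with the company, and results are also summarised with rates and confidence intervals. All of this stands, and it limits the harm. It does not make the verdict one about the added drug.

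**The exclusion.** A reader might infer that the two sections cannot both be followed. That is too strong: the criteria are headed as selected, drug-specific criteria may be added, and "other" can be read as outside the cohort regimen.

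**Conclusion.** The point holds in conditional form. The article fixes one null of 10% for every cohort and allows backbone cohorts without a null of their own, so a positive count there measures the combination and cannot be credited to the added drug alone. The 7.8% carries over to the added drug only if backbone-alone disease control at 16 weeks is 10%. Between assumed rates of 5% and 30%, the chance that an inert add-on is called positive runs from 0.5% to 86%. The inflation becomes material soon after 10% is passed: 14% at 12% and 27% at 15%.

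The arithmetic is exact. The backbone rate is an assumption, and whether any particular cohort is affected cannot be settled from the article. The point concerns selected cohorts only, and leaves the rule as applied to study drugs given without a backbone untouched. The exclusion wording is an unreconciled tension, not a demonstrated contradiction.

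**What to change.** 1. In Study design, Combination and Statistical analyses, state that the 10%/30% rule, with its 7.8% and 85%, describes activity of the study drug only in cohorts without a backbone.

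2. For each backbone cohort, before it opens, set p0 to the 16-week disease control expected on the backbone alone in this population, set p1 accordingly, and recalculate the cutoff at the same 8 + 16 patients. For example, p0 = 20% and p1 = 40% with at least 8 of 24 gives alpha 8.8% and power 80%.

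3. Where no credible p0 can be given, report the cohort descriptively, as activity of the combination, with no verdict on the added drug.

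4. Reconcile the exclusion of other anti-cancer therapy with the Combination section, so that it is clear whether a backbone counts as part of the cohort treatment.

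**Cost.** One paragraph of text, plus one line for each backbone cohort; no extra patients. The real cost is in the target. The rate of interest rises with p0, and under the example cutoff power at a true rate of 30% falls from 86% to 43%. The 80% power applies only to the higher 40% target.
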